While the majority of VTEs are asymptomatic, symptomatic VTEs may result in serious adverse events or death [4]. Therefore, prophylaxis of VTE plays a major role in reducing adverse events and unexpected mortality in patients undergoing neurosurgery. An ACS NSQIP data query for Ochsner Department of Neurosurgery performed on August 1, 2022, for the period of July 1, 2020, to June 30, 2021, yielded incidence rates of VTE as follows: a total of 8 events per 320 total neurosurgery cases for a rate of 2.5%, whereas the predicted rate of VTE was calculated to be 2.83% and the expected rate based on the national average rate of VTE was calculated to be 3.27%. This has resulted in an OR calculation of 0.86 (95% CI 0.52-1.42). When stratified by the type of neurosurgery, the VTE incidence rate was 0.76%, where a VTE event occurred in 1 case out of a total of 132 spine neurosurgery cases. The predicted rate for spine neurosurgery was 1.78% and the expected rate for spine neurosurgery cases was 2.24%, with an OR of 0.77 (95% CI 0.37-1.61). The rate of VTE after neurosurgery for brain tumors at Ochsner was 3.52%, based on 5 cases out of 142 total brain tumor neurosurgery cases. The predicted rate of VTE incidence for patients undergoing neurosurgery for brain tumor was 3.45% and its expected rate was 3.42%, with an OR of VTE incidence among patients after brain tumor neurosurgery of 1.01 (95% CI 0.63-1.63).

Although the incidence of VTE at Ochsner Health Department of Neurosurgery is within the expected range of nationwide data [1-3], the lack of a department- or hospital-based protocol for postoperative VTE prophylaxis results in a heterogeneity of patient care and may contribute to unexpected outcomes. Current practice dictates that individual physicians apply their chosen set of VTE prophylaxis guidelines [17]. This further contributes to a heterogeneity of patient care since most guidelines provide inconsistent recommendations (Multimedia Appendix 1). This creates a gap in patient care that could potentially be bridged through a consistent set of department VTE prevention guidelines, which would aim to diminish patient care variability and reduce the incidence of VTE below the national average rates.

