## Methods

### Overview

This project is well aligned with the Institute of Medicine’s 6 domains of quality health care and was designed according to the Institute for Healthcare Improvement steps to a good QI project [22]. It aims to avoid harm to patients while being effective in providing prophylaxis according to a risk-based approach. Specifically, the adaptive design assessing outcomes and process measures and implementing incremental change on a quarterly basis ensure the safety of this QI project. Our protocol follows the Agency for Healthcare Research 2017 guidelines to ensure patient safety while implementing this protocol [23]. This quality improvement project has been designed and reported in accordance with the SQUIRE 2.0 (Standards for Quality Improvement Reporting Excellence) guidelines. SQUIRE is the most appropriate framework for reporting system-level interventions aimed at improving health care quality, safety, and outcomes. This manuscript addresses all relevant SQUIRE elements [24]. Further, this project is patient-centered and aims to ensure equitable care for patients by consistently including all eligible individuals in the protocol without discriminating based on demographics. Finally, it is a timely and efficient protocol, reducing inconsistent application of variable guidelines and thus potentially avoiding supplies and staff waste. The assessment of the impact of this protocol on VTE incidence is at 12 and 24 months post implementation, with interim analyses every 3 months to ensure continuous quality improvement. The goal is a 50% decrease in the overall VTE incidence in patients undergoing neurosurgery from 2.5% to 1.25%, with a greater decrease in incidence of VTE among patients undergoing neurosurgical procedures for malignant pathology (cranial or spine). Targeting a reduction to 1.25% represents an achievable improvement that aligns with outcomes seen in successful QI initiatives with standardized protocols [25-27]. For example, the Mercy Hospital Springfield Neurosurgery VTE quality improvement initiative found that VTE occurrence rates in neurosurgery decreased from 3.97% at the time of protocol initiation to 0.72% in January 2020 [26]. All patients admitted to the neurosurgery service for postoperative care will be managed according to the new protocol after the implementation date. The incidence of VTE among patients admitted during the previous 12 months will serve as a control.

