
Continuous improvement is built with small incremental changes, using a systematic scientific approach to test their impact and feasibility. The Plan-Do-Study-Act cycle will be used as a model on which to structure tests of change. This includes continuous analysis of errors and successes of the protocol and subsequent protocol adaptation for the duration of the project. Dynamic data will be assessed through a run chart with data points added monthly, but with interim analysis every 3 months. Interim analyses will be discussed before changing the protocol for such quality improvement adaptations. A formal statistical analysis will be performed with a *t* test comparing NSQIP and postprotocol end-of-study VTE rates at both 12 and 24 months post implementation. Stratification based on malignancy and cranial versus spine procedures will also be assessed, as will be the confounding process and balancing measures.

Missing data will be handled through checking at each interim review. Any record missing critical outcome or key covariate information will be excluded from regression analyses. In addition, we will conduct sensitivity analyses to assess the impact of any missing data on VTE rates. Discrepancies will be resolved by consensus and reported, if indicated. Interim analyses with department reports will be performed every 3 months, but every VTE event will trigger an analysis of the variables described in this protocol. Analyses will consider barriers to change and adequacy of the protocol to guide protocol modifications and continuous implementation of improvements.

Additional guidance has been incorporated to inform future iterations of the protocol, including considerations for patients with comorbid atrial fibrillation or those already on antiplatelet therapy [34]. Implemented changes will be made based on recent evidence in the literature [35].

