## Results

The desired timeframe for implementing the Neurosurgery VTE prophylaxis protocol is within 6 months of QI project approval, with 1 month of “adaptation time.” Adaptation time is defined as the time between training the staff involved in the project and starting the timeline for outcomes assessment. Department project approval occurred on February 16, 2023, and the project adaptation time began on August 1, 2023.

Data collection is scheduled for completion in 2024, with analysis expected by March 2025. We anticipate a 50% reduction in VTE incidence (from 2.5% to 1.25%) following implementation of a standardized department-wide cPpx protocol. The primary outcome is the incidence of VTE. To assess whether implementation of the protocol results in a meaningful improvement compared to the standard of care, we will use a pre-post design comparing outcomes in the 12 months before and 12 months after the protocol implementation. We will evaluate differences in VTE rates using chi-square or Fisher exact test to compare the proportion of VTE events pre-implementation versus post-implementation. The justification for the chi-square test is that it is appropriate for large samples with expected counts ≥5. The Fisher exact test will be used as a backup for smaller subgroup comparisons where expected frequencies are low. In order to mitigate confounding, we will use multivariable logistic regression, using VTE occurrence as the dependent variable, with covariates including patient-level and procedural risk factors such as BMI, malignancy, surgery type (cranial vs spine), and immobility. The justification is that regression modeling will help isolate any independent effects of the protocol on VTE rates. To account for continuous secondary outcomes, we will perform stratified subgroup analyses for patients with malignancy, those undergoing cranial versus spine procedures, and those receiving LMWH versus UFH. The justification for this is that we will protect against or identify subgroups that experience differential VTE risk. A stratified analysis will determine if the protocol is equally effective across populations.

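### The stratified analysis is said to determine whether the protocol is equally effective across populations, but no named analysis contrasts its effect between strata, and at the reported volumes even a correct contrast could not establish equality

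*Protocol article*

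**What the plan says.** The Results section of the protocol article sets out the analysis plan. VTE rates are to be compared "using chi-square or Fisher exact test to compare the proportion of VTE events pre-implementation versus post-implementation". For subgroups it adds: "The Fisher exact test will be used as a backup for smaller subgroup comparisons where expected frequencies are low". A multivariable logistic regression, introduced to reduce confounding, is fitted "with covariates including patient-level and procedural risk factors such as BMI, malignancy, surgery type (cranial vs spine), and immobility". Then: "we will perform stratified subgroup analyses for patients with malignancy, those undergoing cranial versus spine procedures, and those receiving LMWH versus UFH". The paragraph closes with the claim at issue: "A stratified analysis will determine if the protocol is equally effective across populations".

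Two other places bear on it. Methods, Selecting Change says: "Stratification based on malignancy and cranial versus spine procedures will also be assessed", without saying how the strata will be compared. Methods, Overview sets an overall goal of a fall from 2.5% to 1.25%, "with a greater decrease in incidence of VTE among patients undergoing neurosurgical procedures for malignant pathology (cranial or spine". A difference in effect between strata is therefore something the project itself expects.

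**The concern.** Whether a protocol is equally effective in two populations is a question about the difference between two effects. A pre-post test inside one stratum speaks only to that stratum. A covariate for malignancy or surgery type lets baseline risk differ, but as a main effect it imposes one common protocol odds ratio on all strata. None of the analyses named estimates the quantity that the closing sentence promises to settle.

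What is at stake is how the subgroup results are read. With few events, most strata will be non-significant whatever the truth. With many events, strata with different baseline rates will often fall on opposite sides of 0.05 even if the relative effect is the same. The first pattern can be mistaken for equal benefit. The second can be mistaken for extra benefit in malignancy or for failure in spine. The primary overall comparison is not affected.

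**Working it through.** **Inputs.** The Introduction, Overview gives, for the benchmark year, "a total of 8 events per 320 total neurosurgery cases", with 1/132 in spine and 5/142 in brain tumour. These reproduce the stated rates: 8/320 = 2.5%, 1/132 = 0.76%, 5/142 = 3.52%. By subtraction, all cases other than brain tumour are 8 − 5 = 3 events in 320 − 142 = 178, and non-spine cases are 8 − 1 = 7 events in 320 − 132 = 188.

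**Assumptions not in the document.** Two-sided 0.05; equal pre and post years of benchmark size, then 3 and 10 times that size; brain tumour as proxy for malignancy and non-spine as proxy for cranial. No counts are given for LMWH versus UFH, so that split is left out.

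**Step 1: power within a stratum.** Exact enumeration of the Fisher test, benchmark size, rate halved:

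| Stratum | Expected events, pre and post | Power |
|---|---|---|
| Brain tumour | 5 and 2.5 | 6.6% |
| Others | 3 and 1.5 | 2.3% |
| Spine | 1 and 0.5 | 0.03% |
| Non-spine | 7 and 3.5 | 11% |

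If VTE were abolished altogether, power would be 38% in tumour and 0.05% in spine. The spine test is almost never significant, whatever the true effect.

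**Step 2: unequal effects that look alike.** Take a 75% cut in tumour and an 8% cut in others, a scenario chosen because it meets the overall goal: 5 × 0.25 + 3 × 0.92 = 4.0 events, and 4/320 = 1.25%. Fisher power is 0.163 and 0.011, so both tests are non-significant in (1 − 0.163) × (1 − 0.011) = 83% of studies.

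**Step 3: equal effects that look different.** Halve the rate in every stratum at 10 times the volume. Apply the article's own rule: chi-square (without continuity correction) where expected counts are at least 5, otherwise Fisher. Power is 0.843 in tumour, 0.617 in others, 0.240 in spine and 0.939 in non-spine. The chance that exactly one of a pair is significant is:
- tumour/others: 0.843 × 0.383 + 0.617 × 0.157 = 0.42
- non-spine/spine: 0.939 × 0.760 + 0.240 × 0.061 = 0.73

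Using Fisher throughout gives 0.46 and 0.78.

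**Step 4: what a correct contrast could show.** The log ratio of odds ratios has SE = √Σ(1/events + 1/non-events) over the four stratum-by-period cells, and its 95% CI extends a factor of exp(1.96 × SE) each way. With rates halved in both strata, at benchmark size:
- Tumour versus others: 1/5 + 1/137 + 1/2.5 + 1/139.5 + 1/3 + 1/175 + 1/1.5 + 1/176.5 = 1.626; SE = 1.275; factor 12.2.
- Spine versus non-spine: 1/1 + 1/131 + 1/0.5 + 1/131.5 + 1/7 + 1/181 + 1/3.5 + 1/184.5 = 3.455; SE = 1.859; factor 38.

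| Volume | Tumour versus others | Spine versus non-spine |
|---|---|---|
| Benchmark | 12.2 | 38 |
| 3 times | 4.2 | 8.2 |
| 10 times | 2.2 | 3.2 |
| Benchmark, 24-month post period | 7.7 | 19.6 |

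Even at 10 times the volume, an estimate of exactly equal effects would be compatible with one odds ratio being about twice (tumour versus others) or three times (spine versus non-spine) the other.

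**The case against.** **An interaction term could sit in a document not shown.** This is correct, and its absence is not the finding. The finding is the article's own sentence, which promises a determination of equality that a contrast could not deliver at benchmark volumes.

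**No rule is stated for reading p-values across strata.** This also stands. A reader might infer that the plan will treat non-significance as proof of equal effect, or will set stratum p-values against one another. The article says neither, and its stated success rule is a point-estimate threshold of at least a 50% reduction overall. The 83%, 42% and 73% figures describe a foreseeable misreading, not a planned one.

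**Stratified data are not uninformative.** Stratum-by-period counts yield a ratio of odds ratios directly, as Step 4 shows, so it would be wrong to say that stratification cannot address the question at any volume. Nor is the malignancy goal without any analysis, since the article stratifies on malignancy in two places. What is lacking is a stated contrast and the precision to support a claim of equality.

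**The figures are illustrative.** This is true. Actual volume is unknown. The malignancy goal covers cranial and spine disease, and the article does not say that the brain tumours were malignant. The goal could also be meant on an absolute rather than a relative scale.

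**Subgroup results drive no success criterion.** True, and the passage saying that results may guide future guidelines concerns the protocol as a whole. This limits the weight of the point without removing it.

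**Conclusion.** The point holds in a limited form. The article claims that a stratified analysis will settle whether effectiveness is equal, while the analyses it names test pre versus post within a stratum or adjust for the stratum as a covariate. No stated analysis contrasts the protocol effect between strata. At benchmark-year volumes a correct contrast would carry a 95% CI of about a factor of 12 (tumour versus others) or 38 (spine versus non-spine) each way, too wide to establish equality. Larger volume narrows the interval but does not make separate stratum tests a valid comparison: at ten times the volume with equal effects they disagree in about 42% and 73% of studies.

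The logical gap does not depend on any assumed figure. The sizes rest on the benchmark counts repeating, equal pre and post years, a halving in every stratum (Steps 1, 3 and 4), and the brain-tumour and non-spine proxies. The article does not support the stronger reading that it plans to infer equality from non-significance. The primary analysis stands; an unsupported subgroup conclusion should be corrected.

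**What to change.** In Results, replace the closing claim about equal effectiveness with text such as:

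> Subgroup analyses are exploratory and will explore whether the protocol effect differs across populations. For each stratum we report pre and post counts and the odds ratio with 95% CI. For malignancy and for cranial versus spine we report the protocol-by-stratum ratio of odds ratios with 95% CI, by a method suited to sparse events, such as Firth logistic regression. Separate stratum p-values will not be used to conclude equal or different effect.

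In Methods, Overview, state that the goal of a greater fall in malignancy will be assessed with the protocol-by-malignancy estimate. Firth regression is one suitable choice, not the only one.

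The cost is two text edits and one interaction term for each of the two stratifiers, using variables already in the model; no further patients or data are needed. The downside is that the subgroup claim becomes exploratory and its intervals will be wide unless volume is far above 320 cases a year.

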**Conclusions:**

It is anticipated that this QI project implementing a department-wide protocol for chemical prophylaxis in patients undergoing neurosurgery will improve the rates of VTE in patients on our service. In addition to a discussion of our results, we provide a comprehensive review of the literature and establish a gap in consistent published guidelines for VTE prophylaxis in patients undergoing neurosurgery. Results from this QI project will provide evidence for the effectiveness of a unified protocol of VTE prophylaxis in this patient group. Furthermore, outcomes from this study may be used as the basis for guideline recommendations and will benefit not only our department but may be used for QI of patient care at other hospitals.

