### Outcomes

The primary outcome measure is the rate of VTE. Benchmark data for the primary outcome is derived from ACS NSQIP VTE rates for Ochsner Neurosurgery and the nationwide ACS NSQIP VTE rate. Benchmarks are 2.5% for Ochsner Neurosurgery and 3.27% for the national incidence rate [3]. Secondary outcome measures include the rate of PE, the rate of symptomatic DVT, and the rate of PE-associated mortality.

Process measures have an impact on the primary and secondary outcomes and will include staffing at the time of VTE diagnosis, volume of patients per resident physician, and the percentage of patients at high risk. Balancing measures include the complexity of patients based on VTE risk and history of VTE despite prophylaxis, medication reconciliations, communication with other services, and volume of patients on the neurological ICU. Procedure and patient risk factors of VTE will be included in the analysis as confounding variables. Unintended consequences such as supratherapeutic anticoagulation or bleeding events, delays in mobilization or surgery due to protocol requirements, or variation in adherence will be monitored as well. The mentioned unintended consequences will be monitored through case review and clinical incident reports, and adjustments to the protocol will be made through the Plan-Do-Study-Act cycle framework.

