Outcomes of this QI project will be reported to the Ochsner Health Department of Neurosurgery as well as hospital administration. Results will also be shared with the scientific and health care quality improvement community. Consideration of “lessons learned” and suggestions for implementing change in order to improve patient outcomes will be made. In addition, consideration of barriers to change and recommendations for improving patient care will be discussed. This project will provide an evidence base for the implementation of the proposed protocol, and its success or failure to achieve the protocol's aims will be equally important for future hospital patient care quality improvement efforts. Considering there are limited neurosurgical society guidelines on VTE prophylaxis in perioperative patients, results from this project can be used to assess the efficacy of our specific protocol in guiding future guidelines specific for patients undergoing neurosurgery. The overarching objective of this quality improvement initiative is to advance the evidence of the effectiveness of anticoagulation prophylaxis in preventing perioperative VTE morbidity and mortality. As previously identified, the determination of whether implementation of this protocol was a success compared to the current standard-of-care success criteria will be measured against a ≥50% reduction in VTE incidence compared to baseline (from 2.5% to ≤1.25%). Secondary success measures include reduction in symptomatic PE and DVT events, and improvement in protocol adherence across clinical teams.

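### Success is judged on the observed VTE rate alone, against a 2020-21 figure that is not the named control, and without reference to the planned tests

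*Protocol article*

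**What the plan says.** **The success rule.** The Results section states that whether implementation was a success "will be measured against a ≥50% reduction in VTE incidence compared to baseline (from 2.5% to ≤1.25" (per cent). No interval, test or error rate is attached. The Methods overview gives the same figures as an aim: "The goal is a 50% decrease in the overall VTE incidence in patients undergoing neurosurgery from 2.5% to 1.25" (per cent).

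**Where 2.5% comes from.** The Introduction reports a registry query for July 2020 to June 2021: "a total of 8 events per 320 total neurosurgery cases for a rate of 2.5" (per cent). The Outcomes section adopts it as the local benchmark: "Benchmarks are 2.5% for Ochsner Neurosurgery and 3.27% for the national incidence rate".

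**The comparison period.** The Results section says "we will use a pre-post design comparing outcomes in the 12 months before and 12 months after the protocol implementation", and the Methods overview likewise names the previous 12 months as the control. Adaptation time began on August 1, 2023, so this control year is later than the registry year.

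**The planned tests.** The Results section adds "We will evaluate differences in VTE rates using chi-square or Fisher exact test to compare the proportion of VTE events" before and after implementation, with multivariable logistic regression for confounding. The section on selecting change plans a t test against the registry rate. None of these is connected to the success decision.

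**The claim.** The abstract's conclusions say "Results from this QI project will provide evidence for the effectiveness of a unified protocol of VTE prophylaxis in this patient group", and that the outcomes may serve as a basis for guideline recommendations.

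**The concern.** There are two separate weaknesses.

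First, a decision made on an observed rate ignores sampling error. With a handful of events per year, a fall from 8 to 4 can easily arise by chance. The project could announce success beside a non-significant primary comparison, and the article does not say which of the two governs the conclusion. That matters because the result is offered as evidence of effectiveness and as input to guidelines.

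Second, the rule states two conditions as if they were one. A reduction of at least 50% and a rate of at most 1.25% are equivalent only if the baseline is exactly 2.5%. If the 12 months before implementation show a different rate, the project has two success criteria and no statement of which applies. This defect needs no assumption about sample size.

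**Working it through.** **Inputs from the article.** Baseline 8/320 (Introduction); cut-off 1.25% (Results); targeted true rate 1.25% (Methods overview).

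**Assumptions.** 320 cases per period, because it is the only annual departmental volume given; 160 to 1280 is shown as a range. Two-sided 5% significance level, because none is stated.

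**1. The plan's own figures.** 8/320 = 0.0250. Half of that is 0.0125, and 0.0125 × 320 = 4. The figures reproduce. At 320 cases, success means at most 4 events.

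**2. Precision of the baseline.** The exact (Clopper-Pearson) 95% CI for 8/320 is 1.09% to 4.87%; the Wilson interval is 1.27% to 4.85%. The target of 1.25% lies just inside the first and just outside the second, so nothing should rest on that comparison. The point is the width.

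**3. Error rates of the fixed cut-off.** Let X be binomial(N, p) and c the largest whole number not above 0.0125 × N. False pass = P(X ≤ c) at p = 0.025. False fail = 1 − P(X ≤ c) at p = 0.0125.

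| N | c | False pass (true 2.5%) | False fail (true 1.25%) |
|---|---|---|---|
| 160 | 2 | 23.4% | 32.3% |
| 320 | 4 | 9.7% | 37.1% |
| 640 | 8 | 2.1% | 40.7% |
| 1280 | 16 | 0.1% | 43.4% |

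False pass also depends on the true baseline. At N = 320 an ineffective protocol passes 23% of the time if the true unchanged rate is 2.0%, and 3.6% if it is 3.0%.

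**4. The rule read as a ratio.** Take two independent binomial periods of 320 and define success as post-period events at or below half of pre-period events. Full enumeration gives a pass probability of 11.1% with no effect (2.5% in both) and 55.5% under a true halving, so false fail is 100 − 55.5 = 44.5%.

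**5. Success beside a null test.** Pre-period 8/320:

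| Post events of 320 | Meets the rule | Fisher p | Chi-square p (uncorrected) |
|---|---|---|---|
| 4 | yes | 0.38 | 0.24 |
| 3 | yes | 0.22 | 0.13 |
| 2 | yes | 0.11 | 0.056 |
| 1 | yes | 0.038 | 0.019 |

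For 8 v 4 the risk ratio is 0.50. The standard error of its logarithm is √(1/8 − 1/320 + 1/4 − 1/320) = 0.607, so the 95% CI is 0.50 × exp(±1.96 × 0.607) = 0.15 to 1.64.

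**6. The two halves of the rule disagreeing (illustrative rates).** Pre-period 1.8%, post-period 1.2%: at or below 1.25%, but the reduction is only 1 − 1.2/1.8 = 33%. Pre-period 3.2%, post-period 1.5%: the reduction is 1 − 1.5/3.2 = 53%, but the rate is above 1.25%.

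**7. Power of the planned comparison.** At 2.5% v 1.25% with 320 per period, enumeration gives 13% for Fisher, 13% for a log-normal risk-ratio interval excluding 1, and 21% for uncorrected chi-square. For 80% power the normal-approximation formula needs about 1848 per period.

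**The case against.** **The volume is unknown.** The article states no post-period number, and 320 is a registry count from 2020-21. A reader might infer that an ineffective protocol passes 1 time in 10 as a fixed property of the plan. The article does not support that: the figure runs from 23% at 160 cases to 0.1% at 1280. Non-significance of an on-target result also depends on volume: 24 v 12 of 960 gives chi-square p = 0.043 (Fisher 0.063), and 32 v 16 of 1280 gives 0.020 (Fisher 0.028). This part of the objection stands.

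**False failure is a feature of any target.** If the true rate equals the cut-off, the pass rate tends to about one half however many patients there are. It would be tempting to say that an effective protocol often fails, but that holds only for one sitting exactly at target. At the 0.72% that the Methods overview cites from another hospital's initiative, the same rule passes 92% of the time at 320 cases. This also stands.

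**It is a quality-improvement aim with tests already planned.** The article calls 50% a goal, plans tests and regression for the pre-post comparison, and concedes limits on causal attribution. That lowers the seriousness. It does not remove the point: the Results section turns the goal into the determination of success, nothing links it to the tests, and the Limitations section covers bias, confounding and missing data but not sampling error.

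**The baseline mismatch is a separate issue.** It can be classed as a control-definition problem, but it sits inside the success rule and makes that rule ambiguous, so it belongs here too.

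**Conclusion.** The concern holds in conditional form. The success rule uses the observed rate alone, is not tied to the planned analysis, and takes its 2.5% from a year other than the named control, so its two conditions can conflict. The lack of a link and the conflict need no numerical assumption.

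The error rates do. At about 320 cases per period and a true baseline of 2.5%, false pass is 9.7%. False fail at a true 1.25% is 37%, and stays between 32% and 43% from 160 to 1280 cases. At that volume, post-period counts of 4, 3 or 2 against 8 would be declared successes without reaching p<0.05. A reader might conclude that the rule makes the project's result worthless. That goes too far: tests and regression are planned, and at higher volumes false passes become rare. What is missing is a statement of which result carries the effectiveness claim. This should be fixed, but it does not invalidate the plan.

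**What to change.** - In the Results section, keep the 50% reduction as the quality target and report it as met or not met, against one named baseline: the 12-month pre-implementation control period. Present the 2020-21 rate of 2.5% as the planning benchmark only.
- State that effectiveness will be claimed only if the 95% CI for the pre/post effect from the planned Results-section analysis excludes no effect. Otherwise report the effect as uncertain, with the interval.
- Give the expected annual volume and the error rates of the target at that volume.
- Soften the sentence in the abstract's conclusions that promises evidence of effectiveness.

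This costs a few sentences and no patients, but two drawbacks should be stated openly. At about 320 cases per period the effectiveness claim would have only about 13-21% power under a true halving, so an inconclusive result is likely; rewording cannot cure a low event count. Using the observed pre-period rate removes the contradiction but makes the target slightly noisier: false pass rises from 9.7% to 11.1%, and false fail from 37.1% to 44.5%.

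### The secondary success measure fixes only a direction for symptomatic PE and DVT, so a protocol with no effect would meet it in about 35-43% of comparisons on a pooled count

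*Protocol article*

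**What the plan says.** The Results section of the protocol article sets two success criteria in consecutive sentences. The primary one has a size: "≥50% reduction in VTE incidence compared to baseline (from 2.5% to ≤1.25" per cent). The secondary one has a direction only: "Secondary success measures include reduction in symptomatic PE and DVT events, and improvement in protocol adherence across clinical teams".

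The Outcomes section defines the same endpoints as rates: "Secondary outcome measures include the rate of PE, the rate of symptomatic DVT, and the rate of PE-associated mortality". There PE is not restricted to symptomatic PE, whereas the Results sentence can be read that way.

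The comparison is between two years: "we will use a pre-post design comparing outcomes in the 12 months before and 12 months after the protocol implementation". A test is named ("We will evaluate differences in VTE rates using chi-square or Fisher exact test"), but for VTE rates. It is not tied to the secondary success measure.

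The Overview in the Introduction gives the only local volume: "a total of 8 events per 320 total neurosurgery cases for a rate of 2.5" per cent. It also says "While the majority of VTEs are asymptomatic, symptomatic VTEs may result in serious adverse events or death", without giving the symptomatic share as a figure.

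**The concern.** A success measure that asks only for a fall is met by one event fewer. With a handful of symptomatic events per year, chance largely decides whether the count goes up, down or stays level.

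Two further points are left open:

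- **Events or rates.** If the two years differ in case volume, a count and a rate can move in different directions.
- **How PE and DVT combine.** The sentence can mean that both must fall, that either may fall, or that their sum must fall. These readings have very different chances of being met when nothing has changed.

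PE and symptomatic DVT are the clinically serious events. The article says that results go to hospital administration and may inform future guidelines. If the primary target is missed, a chance fall of one event could still be reported as a secondary success.

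**Working it through.** **Inputs from the article.** 8 VTE in 320 cases over 12 months (Introduction, Overview); primary target at most 1.25% (Results); 12 months before against 12 months after (Results).

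**Assumptions, because the article gives no figure.** 320 cases in each period. Between 1 and 4 symptomatic events expected per period: there are 8 VTE in total and most VTE are said to be asymptomatic, so 4 is already the upper edge and 8 is a ceiling at which every VTE is symptomatic. PE makes up 30% to 50% of symptomatic events. PE and DVT are independent. The protocol has no effect.

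**Step 1: the article's own figures.** 8/320 = 2.5%. Half is 1.25%, and 0.0125 × 320 = 4 events. Both reproduce.

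**Step 2: primary cut-off with no effect.** P(X ≤ 4) for X ~ Binomial(320, 0.025) = 0.097. If the baseline count is also random and the rule is post at most half of pre, it is 0.111. So about 10%.

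**Step 3: pooled count, equal volumes, no effect.** By symmetry, P(post < pre) = (1 − P(tie))/2, with exact binomial ties.

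| Expected events per period | P(tie) | P(fall), no effect | P(fall), true halving |
|---|---|---|---|
| 1 | 0.309 | (1 − 0.309)/2 = 0.346 | 0.47 |
| 2 | 0.207 | (1 − 0.207)/2 = 0.396 | 0.61 |
| 4 | 0.144 | (1 − 0.144)/2 = 0.428 | 0.73 |
| 8 (ceiling) | 0.102 | (1 − 0.102)/2 = 0.449 | 0.85 |

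At 1 to 4 events the range is 35% to 43%. With 1 expected event the measure hardly separates no effect (35%) from a true halving (47%).

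**Step 4: PE and DVT taken separately.** Let a and b be the no-effect probabilities of a fall in PE and in DVT. Both fall: a × b. Either falls: 1 − (1 − a)(1 − b).

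- Low end, 1 event, 30% PE (0.3 and 0.7 expected): a = 0.200, b = 0.309. Both = 0.062; either = 1 − 0.800 × 0.691 = 0.447.
- High end, 4 events, 50% PE (2 and 2 expected): a = b = 0.396. Both = 0.157; either = 1 − 0.604 × 0.604, about 0.64.

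So 6% to 16% if both must fall, and 45% to 64% if either may fall. At the ceiling of 8 events these reach about 18% and 67%.

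**Step 5: raw counts with unequal volume, no effect.** With 2 to 4 expected pre-period events and 20% fewer post-period cases, the pooled count falls in 47% to 54% of comparisons. With 20% more cases it falls in about 33%. The volume changes are illustrative; the article gives none.

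**Step 6: what a formal test could show.** For 4 events against 0 with 320 per period, two-sided Fisher p = 2 × (320 × 319 × 318 × 317)/(640 × 639 × 638 × 637) = 0.12. For 5 against 0 it is 0.06. Even preventing every symptomatic event would not reach the conventional 5% level at these counts.

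**The case against.** The strongest reply is that this is a list of secondary measures in a quality improvement article, introduced by a word that makes it non-exhaustive. The determination of success is tied in the preceding sentence to the halving of VTE incidence. Tests, error levels and pooling rules for secondary measures are commonly left to an analysis plan. Part of this stands: the sentence is not a confirmatory decision rule, and the absence of a named test is not itself the fault. But the article does state a success criterion, gives the primary one a size and this one none, and uses a different quantity from its own Outcomes section. Those are features of the text, not details left out by condensing.

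Three stronger readings are tempting and are not supported:

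- **That a protocol with no effect succeeds as often as a coin toss, or more.** At equal volume a single count falls with probability strictly below 50%, because ties are not falls. Going above 50% needs the either-endpoint reading, the least literal one given that the sentence joins PE and DVT with 'and', or an assumed drop in volume. If both must fall, the figure is at most 16% in the range used here.
- **That these outcomes have no denominator.** That is true only of the one sentence; the Outcomes section defines rates. The fault is a mismatch between the two places.
- **That 4 to 8 symptomatic events should be expected.** With 8 VTE in total and most VTE described as asymptomatic, that range starts where the article's own description ends.

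It is also fair to object that a rule allowing a claim only when the interval excludes zero would be nearly unattainable. That is right, and it is why the fix makes the measure descriptive.

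**Conclusion.** The point holds in a limited form. The secondary success measure has a direction but no size or uncertainty limit, speaks of events where the Outcomes section speaks of rates, and leaves open how PE and DVT combine. With no effect it would be met in about 35-43% of comparisons on a pooled count, roughly four times the 10% or so for the primary cut-off. Depending on which unstated reading is used, the figure runs from about 6% to about 64%.

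This rests on 320 cases per period, 1 to 4 expected symptomatic events, a PE share of 30-50% and independence of PE and DVT. The symptomatic count and the PE share are assumptions, because the article gives neither. The consequence is modest, since the measure is secondary, but the correction is cheap. The part of the sentence on protocol adherence was not assessed.

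**What to change.** In the Results section, replace the reduction in events by wording such as: 'For PE and for symptomatic DVT, separately and combined, we will report the difference in rate per eligible case between the 12 months before and the 12 months after implementation, with an exact 95% confidence interval. These comparisons are descriptive. A fall whose interval includes zero will not be called a success.' Use the same endpoint definitions here and in the Outcomes section, including whether PE means all PE or symptomatic PE only.

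The cost is wording only; no additional data are needed. The downside is that at these counts a secondary success can almost never be claimed, since even 4 events against 0 gives p = 0.12. The protocol should say this openly, so that the lack of a claim is not read as evidence that the protocol failed.
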